# The Availability and Safety Study of Remimazolam Besylate for Injection on Sedation of ERAS Patients Under Mechanical Ventilation in ICU: Protocol for a Randomized, Open-Label, Controlled Trial

**DOI:** 10.3389/fmed.2021.735473

**Published:** 2021-11-05

**Keywords:** Remimazolam Besylate, ERAS, mechanical ventilation, intensive care unit, sedation

## Abstract

**Introduction:** The most common physiological and psychological disorders associated with critical care patients are pain and anxiety. Sedatives and analgesics are commonly used to relieve these symptoms. However, the adverse effects of sedatives and analgesics are common and inevitable. As a new type of sedative drug, limited number of trials are available to evaluate Remimazolam Besylate's availability and safety compared with propofol.

**Methods:** This study is a single center, randomized, open-label, controlled trial. A total of 84 patients who meet ERAS criteria and receive mechanical ventilation in ICU, aged ≥18 years old will be included. Patients will be randomized (1:1) into two groups: Remimazolam Besylate group and Propofol group. The Primary outcomes includes satisfaction rate of sedation and incidence rate of major clinical events. Secondary outcomes including incidence of delirium, time to weaning and extubation, Difficulty of nursing RASS, BIS and PI, 28-days survival, side-effect and vital signs during medications, total dose and dose per kilogram body weight of analgesic and sedatives and incidence of rescue therapy in experimental group.

**Ethics and Dissemination:** This trial has been approved by the ethics boards of Peking Union Medical College Hospital. Recruitment began in January 2022 and will continue until June 2022. Dissemination plans include presentations at scientific conferences, scientific publications, stakeholder engagement efforts and presentation to the public via lay media outlets.

**Clinical Trial Registration:**
www.ClinicalTrials.gov, identifier: NCT04947345

## Introduction

### Background

Pain and anxiety are the most common physiological and psychological disorders associated with critical care patients. Organ dysfunction caused by severe diseases in ICU patients, combined with environment and various invasive treatments can produce strong pain and psychological stress, which may directly affect the respiratory, circulatory and immune functions of patients (1). Analgesia, sedation and humanistic care can reduce stress response, relieve tension, and reduce the incidence of delirium (2, 3). However, irregular analgesia and sedation treatments are not only ineffective, but may also cause adverse reactions.

Currently commonly used sedative drugs in clinical practice include midazolam, propofol, and dexmedetomidine. Midazolam has a good sedative effect and has little effect on the respiratory and circulation. At the same time, it can be antagonized by flumazenil. However, midazolam has a slower onset of action and a longer awakening time. As the infusion duration increases, it is easy to cause accumulation. Although propofol has a good sedative effect and can wake up quickly, it is prone to respiratory/circulation depression, and no antagonist was found suggest potential risks. Dexmedetomidine has a good sedative effect and has a small effect on respiratory, however, the pharmacological mechanism of dexmedetomidine determine its slow onset and negative effect on heart rate and blood pressure.

As a new type of sedative drug, Remimazolam can be rapidly metabolized by tissue esterase in the body to produce inactive metabolites, so that its sedative effect will quickly fade. In a phase I single-center randomized double-blind study, researchers found that Remimazolam can reach the peak blood concentration 1 min after intravenous infusion, the metabolism is rapid, and continuous infusion has almost no accumulation (4). Studies also show that Remimazolam has little effect on respiratory/circulation system. Blood pressure and heart rate fluctuate little during the injection of Remimazolam (5). The pharmacokinetics research on healthy volunteers shows its clearance is not related to weight, which provide more sedative option for high weight patients in ICU.

The PK/PD study of Remimazolam in healthy people has been carried out lately (6, 7). As for clinical applications, the effectiveness and safety evaluation of Remimazolam was carried out in phase IIb clinical study of colonoscopy sedation in 2015 (8), bronchoscopy sedation in 2019 (9), anesthesia induction and maintenance in 2020 (10). These studies showed Remimazolam has certain advantages in the effectiveness and safety of sedation.

### Objectives

This study is designed to verify the hypothesis that compared with propofol, Remimazolam Besylate for Injection has non-inferiority availability and safety effect on sedation of ERAS patients under mechanical ventilation in ICU. The primary outcome is satisfaction rate of sedation and incidence rate of major clinical events. For availability evaluation, the secondary outcome includes incidence of delirium, time to weaning and extubation, difficulty of nursing, RASS, BIS and PI during medications. For safety evaluation, the secondary outcome includes 28-days survival, side-effect and vital signs during medications, total dose and dose per kilogram body weight of analgesic and sedatives and incidence of rescue therapy in experimental group.

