## Outcomes

### Primary Outcomes

Validity endpoint is satisfaction rate of sedation, which equals to proportion of time in target sedation range (RASS score, 0 to −3) without use of rescue therapy of the total duration of study drug infusion. Safety endpoint is the incidence of hypotension (SBP < 90 mmHg), the incidence of hypoxia (SpO_2_ < 90%), and the incidence of bradycardia (HR < 75% baseline HR or HR < 50 bpm).

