## Sample Size Planning

In this study, propofol was used as a positive control. The hypothesis is compared with propofol, Remimazolam Besylate for Injection has non-inferiority satisfied rate of sedation on ERAS patients under mechanical ventilation in ICU. Setting inspection level: α = 0.05, 1–β = 80%, the non-inferiority threshold is 10%. Subjects in experimental group and control group is 1:1. According to the results of previous clinical trials, the target sedation rate of the propofol group is 82% (11), assuming that the target sedation rate of the Remimazolam Besylate group is 92%, a total of 70 subjects (35 for experimental group and 35 for control group each) should be enrolled to meet inspection level. Sample size calculations allow for 15% loss of cases, a total of 84 subjects (42 for experimental group and 42 for control group each) are enrolled in this clinical trial.

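### The Objectives hypothesise non-inferior safety, but the plan's only margin and sample size are for sedation, so there is no stated standard for judging the safety claim

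*Protocol article*

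**What the plan says.** Four sections of the protocol article bear on this point.

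- **Objectives.** The hypothesis covers two things at once: "Remimazolam Besylate for Injection has non-inferiority availability and safety effect on sedation of ERAS patients under mechanical ventilation in ICU". The same section continues: "The primary outcome is satisfaction rate of sedation and incidence rate of major clinical events".
- **Primary Outcomes.** The safety half is defined by three events: "Safety endpoint is the incidence of hypotension (SBP < 90 mmHg), the incidence of hypoxia (SpO_2_ < 90%), and the incidence of bradycardia". No margin accompanies them.
- **Sample Size Planning.** The hypothesis is restated without safety: "Remimazolam Besylate for Injection has non-inferiority satisfied rate of sedation on ERAS patients under mechanical ventilation in ICU". The design values are "α = 0.05, 1–β = 80%, the non-inferiority threshold is 10" per cent. The rates are also for sedation: "the target sedation rate of the propofol group is 82" per cent, against an assumed 92% on remimazolam. This gives 35 per arm, raised to 42 per arm for 15% loss.
- **General Statistics.** Proportions are compared by chi-square or Fisher's exact test, and effects count as significant at p < 0.05.

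**The concern.** Objectives and Sample Size Planning print two different hypotheses. One claims non-inferiority for sedation and safety, the other for sedation only. A non-inferiority claim has meaning only relative to a margin, and no safety margin, expected safety rate or safety power is stated.

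The tests described for proportions ask whether the arms differ. In a trial of this size such a test can easily be non-significant while a large excess of events remains possible. If that result were set against the hypothesis in the Objectives, it could be taken as support for non-inferior safety. The events concerned are hypotension, hypoxia and bradycardia in ventilated patients, so a mistaken reading would matter.

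**Working it through.** **1. Reproduce the stated sample size from sedation inputs only.**

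Inputs from Sample Size Planning: 82% (propofol), 92% (remimazolam), margin 10 points, α = 0.05, power 80%, loss 15%. The sidedness of α is not stated, so both values are tried.

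n per arm = (z₁₋α + z₁₋β)² × [p₁(1−p₁) + p₂(1−p₂)] / (margin + p₂ − p₁)²

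- Variance term: 0.82 × 0.18 + 0.92 × 0.08 = 0.1476 + 0.0736 = 0.2212
- Distance from the margin: 0.10 + 0.10 = 0.20, squared 0.04
- One-sided 0.05: (1.645 + 0.842)² × 0.2212 / 0.04 = 34.2, so 35 per arm. Then 35 / 0.85 = 41.2, so 42 per arm and 84 in total. This matches the plan.
- One-sided 0.025: 43.4, so 44 per arm, and 52 after loss. This does not match.

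The planned number follows from the sedation inputs at one-sided 0.05. No safety input is needed to reach it.

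**2. Precision for a safety incidence.**

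The article gives no safety rates, so equal true rates of 10%, 20% and 30% in both arms are assumed. The base is the 35 evaluable per arm that the plan expects, not the 42 enrolled.

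SE = √[2p(1−p)/35]; half-width of the 95% CI = 1.96 × SE

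The plan states no safety margin. The power columns borrow the 10-point sedation margin for illustration only: power = Φ(0.10/SE − z₁₋α).

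| Assumed rate | SE | 95% CI half-width | Power, one-sided 0.05 | Power, one-sided 0.025 |
|---|---|---|---|---|
| 10% | 0.0717 | 14.1 points | 40% | 29% |
| 20% | 0.0956 | 18.7 points | 27.5% | 18% |
| 30% | 0.1095 | 21.5 points | 23% | 15% |

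**3. How far this depends on the assumptions.**

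With 35 per arm, one-sided 0.025 and the borrowed 10-point margin, power = Φ[(0.10 + p_C − p_T)/SE − 1.96], where p_C is the propofol rate, p_T the remimazolam rate and SE = √{[p_C(1−p_C) + p_T(1−p_T)]/35}:

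- 30% on propofol, 20% on remimazolam: SE 0.1028, power 49%
- 30% against 15%: SE 0.0982, power 72%
- 30% against 10%: SE 0.0926, power 90%

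A wider margin also helps. With equal rates of 5% and a 15-point margin, power on a single endpoint is 82%.

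**4. What a non-significant difference can hide.**

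Take assumed counts of 12/35 on remimazolam and 7/35 on propofol (34% and 20%). Fisher's exact test gives p = 0.28. The difference is 14.3 points with SE 0.1049, so the Wald 95% CI runs from −6 to +35 points. The test finds no difference, yet the data are compatible with an excess of 35 points.

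**The case against.** The strongest reply is that the working hypothesis is the one in Sample Size Planning, the only section with a margin, α and power, and that the Objectives are just a loosely worded aim. Sizing a trial on efficacy and estimating safety alongside is ordinary practice, and an article may leave analysis detail to a fuller document. Much of this is fair. Had safety been described as estimated only, there would be nothing to raise. But the Objectives call the statement a hypothesis to be verified and name the safety events as primary. The conflict is between two printed statements, and analysis detail elsewhere would not remove it.

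A second reply is that the low power rests on the reviewer's rates and margin. This stands. The Introduction describes remimazolam as having little effect on respiration and circulation and propofol as prone to depress both, so equal rates are not the protocol's own premise. Step 3 shows that a large advantage could give adequate power on one endpoint.

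A reader might also infer an inflated type I error, with several primary comparisons each tested at 5% and any one success claimed. The document does not support that. No section says that one success suffices, the hypothesis joins sedation and safety with an 'and', and requiring all parts to succeed does not inflate type I error. The three events are also unlikely to be independent. No multiplicity figure is claimed here.

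Finally, no section says that a non-significant safety result will be read as non-inferiority. That is a risk left open by the wording, not a stated intention.

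**Conclusion.** The point holds as a mismatch between the claim and the design. Non-inferior safety is part of the stated hypothesis, yet no margin is given for it, the sample size reproduces exactly from sedation inputs, and the tests described cannot establish it. This part needs no assumption.

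The size of the shortfall is conditional. With equal rates of 10% to 30% and 35 evaluable per arm, a risk difference would be known only to within about 14 to 21 points. The 27.5% and 18% power figures hold for 20% rates and a borrowed 10-point margin.

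It would go too far to say that the trial could never support a safety conclusion: a wide margin with rare events, or a large true advantage, could suffice on one endpoint. It would also go too far to say that the safety events must lose their primary status. The fault lies in the non-inferiority wording attached to them.

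**What to change.** - **Objectives:** limit the non-inferiority hypothesis to the sedation satisfaction rate, so that it agrees with Sample Size Planning.
- **Primary Outcomes and General Statistics:** state that hypotension, hypoxia and bradycardia will each be reported as a risk difference with a 95% confidence interval, and that a non-significant difference will not be interpreted as non-inferior or equal safety. They can remain listed as primary safety outcomes.

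If the sponsor wants to keep a formal safety claim, the alternative is to pre-specify one safety endpoint or a composite, with a justified margin, an expected rate, a decision rule and a matching sample size. That would probably need more patients. For example, equal 20% rates, a 10-point margin, one-sided 0.025 and 80% power need 252 evaluable per arm (2 × 0.16 × 7.85 / 0.01 = 251.2).

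**Cost of the recommended change:** the trial gives up a formal claim of non-inferior safety. No new patients are needed. The article sends substantial amendments to the ethics committee before implementation, and a change to the stated hypothesis may count as one.

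### The objective claims non-inferior safety, but the only margin, assumed rates and sample size are for sedation satisfaction, so the design does not reliably support a safety non-inferiority conclusion

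*Protocol article*

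**What the plan says.** The protocol article's Objectives section states one hypothesis with two halves: compared with propofol, "Remimazolam Besylate for Injection has non-inferiority availability and safety effect on sedation of ERAS patients under mechanical ventilation in ICU". The same section makes the incidence of major clinical events a primary outcome beside the satisfaction rate of sedation. Primary Outcomes then gives the safety endpoint as three separate incidences: hypotension, hypoxia and bradycardia.

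Sample Size Planning states a narrower hypothesis: "Remimazolam Besylate for Injection has non-inferiority satisfied rate of sedation on ERAS patients under mechanical ventilation in ICU". The design values follow directly: "Setting inspection level: α = 0.05, 1–β = 80%, the non-inferiority threshold is 10" per cent. The rates are also for sedation: "the target sedation rate of the propofol group is 82" per cent, and "assuming that the target sedation rate of the Remimazolam Besylate group is 92" per cent. These give 35 evaluable patients per arm, raised to 42 per arm for 15% loss.

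General Statistics lists comparisons of proportions and means, regression and survival methods, with significance at p < 0.05. The article gives no safety margin, expected safety incidence, safety power, or rule for combining the three incidences.

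**The concern.** The two sections disagree on what the trial sets out to show. One promises non-inferiority on sedation and on safety; the other defines and sizes non-inferiority for sedation only. The safety half has no margin in the article, and the named tests ask whether the arms differ, which is not a non-inferiority question.

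At stake is how the safety results may be worded. In a small trial a difference test is often non-significant even when there is a real excess of events. With an objective that already speaks of non-inferior safety, such a result could easily be reported as support for it.

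**Working it through.** **1. The plan's own figure.** Inputs from Sample Size Planning: rates 0.82 and 0.92, margin 0.10, α = 0.05, power 80%, 1:1 allocation. The sidedness of α is not stated.

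n per arm = (z₁₋α + z₁₋β)² × [p_C(1−p_C) + p_T(1−p_T)] / (margin + p_T − p_C)²

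= (1.645 + 0.842)² × (0.1476 + 0.0736) / (0.20)² = 34.2, so 35 per arm.

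With 15% loss, 35 / 0.85 = 41.2, so 42 per arm. Both stated figures reproduce with a one-sided α of 0.05. One-sided 0.025 would give 44 per arm and does not match. The size is therefore wholly a sedation calculation. It also depends on a 10-point advantage for remimazolam: with both rates at 82%, the same formula needs 183 per arm.

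**2. The same method applied to one safety event.** Assumptions, none of them in the documents: a 10-point margin borrowed from sedation; equal true incidence p in both arms; p from 2% to 30%; all 42 per arm evaluable.

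SE = √(2p(1−p)/42); power = Φ(0.10/SE − z); 95% CI half-width = 1.96 × SE

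| p | SE | Power, one-sided 5% | Power, one-sided 2.5% | Half-width (points) |
|---|---|---|---|---|
| 2% | 0.031 | 95% | 90% | 6 |
| 5% | 0.048 | 68% | 56% | 9 |
| 10% | 0.065 | 45% | 33% | 13 |
| 20% | 0.087 | 31% | 21% | 17 |
| 30% | 0.100 | 26% | 17% | 20 |

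Example at p = 10%: 0.10/0.0655 − 1.645 = −0.117, and Φ(−0.117) = 0.453.

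The normal approximation is weak for rare events. Exact binomial enumeration at 2% and one-sided 5% gives 83% (Newcombe limit) to 89% (Wald limit). At 10% it gives 42% to 48%, so the pattern stands. With 35 evaluable per arm, power is lower: 40%, 27% and 23% at 10%, 20% and 30% by the normal formula.

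**3. Margin that 42 per arm supports with 80% power** (one-sided 5%, equal rates): (1.645 + 0.842) × SE = 11.8 points at a 5% incidence, 16.3 at 10%, 21.7 at 20% and 24.9 at 30%.

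**4. If remimazolam is truly safer.** Power = Φ((0.10 + p_C − p_T)/SE − 1.645), with SE = √([p_C(1−p_C) + p_T(1−p_T)]/42). Propofol against remimazolam:

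- 20% against 10%: 83%
- 30% against 15%: 87%
- 40% against 20%: 92%
- 30% against 20%, a smaller relative advantage: 69%

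**5. What the named tests would show if remimazolam were worse.** Exact enumeration at 42 per arm, two-sided 5%, rates assumed; chance of a significant result:

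| Propofol | Remimazolam | Chi-square | Fisher |
|---|---|---|---|
| 10% | 20% | 26% | 18% |
| 10% | 25% | 46% | 36% |
| 20% | 35% | 34% | 26% |
| 5% | 25% | 78% | 68% |
| 10% | 40% | 92% | 87% |

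In these examples, excesses of 10 to 15 points are more often missed than found; the larger ones are usually found.

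All these figures are for a single event. Success required on all three incidences would be harder than success on one.

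**The case against.** A reader might infer that 42 per arm cannot show non-inferior safety at any margin near 10 points, so that the conclusion is closed to this trial. The documents do not support that. Low power is not impossibility, and the result turns on incidences that the article does not give. For events near 2% a 10-point margin is adequately powered at one-sided 5%, and at 5% a margin of about 12 points reaches 80%. The Background describes propofol as prone to respiratory and circulatory depression and remimazolam as having little such effect, so a true advantage is a reasonable scenario, and a large one restores the power. These points stand.

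A reader might also infer that the investigators will take a non-significant safety p-value as proof of non-inferior safety. No section says so; the wording of the objective leaves the risk open, and that is all that can be claimed.

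Finally, this is a condensed article. A safety margin and decision rule may sit in the full protocol or the analysis plan, so their absence here is not in itself a fault. Sizing a trial on one endpoint is also ordinary practice. What remains is that the article does state a hypothesis, a margin and a sample size, and its two statements of the hypothesis differ in scope. A margin held elsewhere would not alter the fact that the stated sample size was derived from sedation alone.

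**Conclusion.** The point holds as a contradiction in the scope of the hypothesis, with a consequence for what may be concluded. Objectives claims non-inferiority for sedation and safety; Sample Size Planning defines, margins and sizes it for sedation satisfaction only; and the tests named in General Statistics do not assess non-inferiority.

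If safety incidences are equal and between 10% and 30%, power at a 10-point margin is about 45% down to 26% for one event. It is better for rare events, and for commoner events if remimazolam is substantially safer. The margin, the incidences and the equality of risk are assumptions, so the size of the shortfall is conditional on them. Non-inferior safety is a conclusion that the design does not reliably support, not one that it rules out.

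**What to change.** Reconcile Objectives with Sample Size Planning by limiting the non-inferiority hypothesis to the satisfaction rate of sedation. State that hypotension, hypoxia and bradycardia will each be reported as a risk difference with a 95% confidence interval, and that a non-significant difference will not be read as non-inferior safety. If expected precision is given, show it as a range over assumed incidences, as in the half-width column above (about 6 points at 2% to 20 points at 30%), not as one fixed figure.

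If the sponsor wishes to keep the safety claim, the alternative is to state and justify a margin, expected incidences and a rule across the three events, and to size for them. With equal incidences of 10% to 30% and a 10-point margin, that means about 112 to 260 per arm (one-sided 5%) for one event.

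The first route changes only the wording of the objective and the reporting rule and needs no more patients. Its cost is a less favourable safety claim.

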## Methods and Analysis

### Trial Design/Study Setting

A prospective, single-center, randomized controlled trial in patients who meet the inclusion criteria. This study is performed in Intensive Care Unit (ICU) in Peking Union Medical College Hospital. All staffs that participate in this study have professional licenses and certificated in Peking Union Medical College Hospital. The approval number of ethics committee of Peking Union Medical College Hospital is 20-JS-2814.

### Eligibility Criteria

#### Inclusion Criteria

Meet criteria of enhanced recovery after surgery (ERAS);Mechanical ventilated when enrolled and have estimation of more than 10 h of mechanical ventilation in ICU;Aged between 18–75 years old and 18 ≤ BMI ≤ 30 kg/m^2^;Clearly know the purpose and objective of this clinical study and voluntarily enrolled.

Criteria of ERAS: (1) without dysfunction of nervous system or Glasgow Coma Score >12; (2) a satisfied glucose level (random blood glucose <11.1 mmol/L during screening stage) for diabetes mellitus patients; (3) Without acute coronary syndrome in recent 6 months; (4) Without bradycardia and third-degree atrioventricular block (except for patients with pacemaker) during screening stage; (5) systolic blood pressure >90 mmHg with no usage of vasoactive agent during screening stage; (6) without mental illness (schizophrenia, depressive disorder), cognitive dysfunction (identified by MMSE), epilepsy, history of abuse of psychotropic, or anesthesia medication; (7) without disorder of coagulation function (PT/INR/APTT > 1.5 × upper limit), bleeding tendency (active peptic ulcer), under treatment of thrombolysis and anticoagulant; (8) without disorder of liver function (ALT/AST > 2 × upper limit and total bilirubin > 1.5 × upper limit); (9) without disorder of renal function (Creatine or BUN/Urea > 1.5 × upper limit); without dialysis patients.

